### Trial design

This study is a randomised controlled trial with a duration of 6 months. After signing informed consent, eligible participants will be randomised to eTRE-MD or N/B. Details of the informed consent form are presented in online supplemental file 1. Outcome parameters will be measured at baseline, 3 months and 6 months. Figure 1 shows the flowchart of this study.

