### Sample size and recruitment

Little is known in the literature about the effect of N/B on liver fibrosis. A recent study showed a decrease in LSM from 4.67 kPa to 4.14 kPa after 6 months of N/B use.^31^ The relevance of this finding is unclear, since LSM values <7.0 kPa are considered to be not clinically relevant. Studies in which participants followed a Mediterranean diet for 6 months show varying outcomes. Two studies showed that it has an average decrease of 0.4 to 2.1 kPa in liver fibrosis.^32 33^ To calculate the effect size, we took a mean difference of the two dietary studies (1.3 kPa), the mean of the N/B group (0.5 kPa) and an SD of 1.0 kPa, which is based on expert opinion due to lack of evidence in the literature. This leads to an effect size of 0.8 kPa. In this study, we will perform a two-sided hypothesis test to assess whether there is a difference in LSM after 6 months between the eTRE-MD group and N/B group. The null hypothesis (H0) states that there is no difference in LSM between the groups, while the alternative hypothesis (H1) assumes a difference of 0.8 kPa or more. Based on an effect size of 0.8 kPa with an SD of 1.0 kPa, a significance level of 0.05 and power set to 0.80, we calculated that 29 participants per group are needed. Assuming a drop-out of 10%, inclusion will be 70 participants (35 participants per group). Unpublished data from ongoing research within our department show that about 20% of people with one or more cardiometabolic risk factors in the Netherlands have a transient elastography result >7.0 kPa. This means that to include 70 patients, we will need to screen about 350 people. It is likely that the planned number of participants can be recruited as 3000 people with cardiometabolic risk factors are seen at the outpatient clinic every year. The patient population not treated at the hospital will be referred by the general practitioner when MASLD is suspected.

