### Randomisation

After signing informed consent, participants will be randomised to either the eTRE-MD group or N/B group. A 1:1 randomisation will be performed via a data management system (Castor Electronic Data Capture (EDC), Amsterdam, The Netherlands) in blocks of 2, 4 and 6. Results from the randomisation will be communicated to the participant after the baseline measurements. The resulting randomisation list will be managed by the secretary of the department of Internal Medicine in the Franciscus hospital. Participant blinding will not be done, as blinding is impossible considering this type of intervention. However, the first preliminary statistical analyses of the primary outcome will be performed by an independent statistician, blinded for the allocation.

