### Statistical methods

All analyses will be conducted according to the intention-to-treat and per protocol principle. To be included in the per protocol analysis, a participant is required to have at least data available for two time points (baseline and T1 or T2) and to achieve 80% or higher adherence. Participants of the eTRE-MD group are considered adherent to the dietary protocol if they restrict their daily food intake to a window of less than 10 hours—specifically between 7:30 AM and 6:30 PM—on at least 5 days per week. Additionally, they must maintain a daily caloric intake that is at least 400 calories below their estimated energy requirement. Participants of the N/B group are considered adherent to the medication protocol if they consistently take a minimum of two tablets per day, with the exact dosage adjusted according to individual tolerance levels. These adherence data will be used to classify participants for the per protocol analysis and to explore the impact of medication compliance on treatment outcomes. All other non-compliant participants will be excluded from the per protocol analysis. Normality of the data and homogeneity of variances will be tested using Shapiro-Wilks test and Levene’s test. For numerical data, we will use the mean (in case of normal distribution) and median values (in case of non-normal distribution), with respectively the SD and IQR as measures of dispersion.

The primary outcome will be defined as the absolute change in liver fibrosis during 6 months. The difference in liver fibrosis change between the eTRE-MD group and N/B group will be analysed with a linear mixed model adjusted for baseline, with independent variables treatment arm, time point (T1 and T2), and the interaction between treatment arm and time point. The estimated difference between treatment arms in the liver fibrosis change at T2 (6 months) will be calculated using the estimated marginal means. Mixed modelling can efficiently handle data with missing and unbalanced time-points. It corrects for bias when absence of data is dependent on characteristics that are present in the models (missing at random, MAR). The secondary outcomes will be analysed with a linear mixed model adjusted for baseline, with independent variables treatment arm, time point (T1 and T2), and the interaction between treatment arm and time point. The estimated difference between treatment arms will be calculated using the estimated marginal means.

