To account for heterogeneity in metabolic profiles, cardiometabolic condition (type 2 diabetes, hypertension, dyslipidaemia or obesity) will be included as a covariate in all primary and secondary outcome analyses. Outcomes will be analysed using linear mixed models with treatment arm, time point (T1 and T2), and their interaction as fixed effects, adjusted for baseline values. An interaction term between treatment arm and cardiometabolic condition will be explored to assess potential differential treatment effects across subgroups. Given the limited sample size, stratified analyses will not be performed unless sufficient power is available. Participants with multiple conditions will be included in the overall model and appropriately coded for subgroup membership. Sensitivity analyses may be conducted to evaluate the robustness of findings in overlapping vs non-overlapping subgroups.

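### The primary mixed model, as written, uses one baseline LSM slope for months 3 and 6, although the primary estimate is the month-6 contrast; a baseline-by-time term is a cheap safeguard

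*Protocol article*

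**What the plan says.** The article's Trial design section sets three measurement occasions: "Outcome parameters will be measured at baseline, 3 months and 6 months". Under Statistical methods, the primary model is given as: "linear mixed model adjusted for baseline, with independent variables treatment arm, time point (T1 and T2), and the interaction between treatment arm"; the last term is arm by visit. The primary estimate comes from one visit of that model: "The estimated difference between treatment arms in the liver fibrosis change at T2 (6 months) will be calculated using the estimated marginal means". The last paragraph of the same section repeats the list for all primary and secondary outcomes, "linear mixed models with treatment arm, time point (T1 and T2), and their interaction as fixed effects, adjusted for baseline values". It also adds cardiometabolic condition as a covariate and an exploratory arm-by-condition interaction.

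Interactions are therefore named where they are intended, and baseline by time point is not among them. It is not excluded either. The covariance structure is not given, and the statistical analysis plan is not shown.

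**The concern.** With a single baseline coefficient, the model assumes that a 1 kPa difference at baseline predicts the same difference at month 3 as at month 6. The primary estimate uses only month 6, but its baseline correction uses a slope pooled over both visits. If the two slopes differ, the month-6 arm difference is corrected by the wrong amount for whatever baseline imbalance randomisation produced. Two things could follow: a standard error larger than the same data allow, and a residue of chance imbalance in the reported estimate.

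The section also relies on the mixed model to deal with data missing at random, given the characteristics in the model. That protection depends on the model for the mean being right, including how baseline enters it.

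**Working it through.** **The plan's own figure.** Sample size and recruitment states "Based on an effect size of 0.8 kPa with an SD of 1.0 kPa, a significance level of 0.05 and power set to 0.80" and gives 29 per group.
- The two-sided normal formula gives 2 × (1.96 + 0.84)² × 1.0² / 0.8² = 24.5, so 25 per group. The t-test gives 26.
- 29 is not reproduced directly, although 26 / 0.9 = 28.9 would reach it. The difference is on the safe side: 29 per group gives about 85% power.
- 35 per group less 10% leaves about 31 completers, which is the number used below.

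None of this bears on the point.

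**What the shared slope is.** Let b3 and b6 be the baseline slopes at months 3 and 6, s3 and s6 the residual SDs, and r their correlation. With complete data and generalised least squares, the shared slope is w·b3 + (1 − w)·b6, where

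w = (s6² − r·s3·s6) / (s3² + s6² − 2·r·s3·s6).

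- Equal residual SDs: w = 0.50 for any r. A random-intercept model gives the same.
- s3 = 0.8·s6, r = 0.5: w = 0.60 / 0.84 = 0.71.
- s3 = 0.8·s6, r = 0.7: w = 0.44 / 0.52 = 0.85.

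Analysing change rather than the LSM value subtracts 1 from both slopes and leaves their gap unchanged.

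**What reaches the month-6 contrast.** The error in the slope is w × (b3 − b6). Multiplied by the baseline difference between arms, it gives the uncorrected part. The variance ratio (shared over visit-specific slope) is roughly 1 + (w × gap × SD_baseline / s6)², less a small amount for estimating the extra slope.

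**Assumed inputs, because the document gives none.** Baseline SD is 1.2 to 1.9 kPa; a uniform spread over the eligibility range of 7.0 to 13.6 kPa gives 6.6/√12 = 1.9. The ratio s3/s6 is 0.8 to 1, and r is 0.5 to 0.7. The SD of the 6-month change is 1.0, so s6² = 1 − ((1 − b6) × SD_baseline)².

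Ends of the range by formula, then by simulation (31 per arm, 6,000 runs per setting):
- Gap 0.2 (slopes 0.95, 0.75), SD 1.2, w = 0.50: s6² = 0.91; 1 + 0.12²/0.91 = 1.016; simulated 1.013.
- Gap 0.2, SD 1.9, w = 0.846: s6² = 0.774; 1 + 0.3215²/0.774 = 1.13; simulated 1.117.
- Gap 0.3 (slopes 0.9, 0.6), SD 1.2, w = 0.50: s6² = 0.770; 1 + 0.18²/0.770 = 1.04; simulated 1.030.
- Gap 0.3, SD 1.9, w = 0.846: s6² = 0.422; 1 + 0.482²/0.422 = 1.55; simulated 1.522.

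A 1-SD chance imbalance in mean baseline LSM is SD_baseline × √(2/31), which is 0.30 to 0.48 kPa. The part carried into the contrast is w × gap × imbalance.

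| Slope gap | Variance ratio (simulated) | Carried by a 1-SD imbalance (kPa) |
|---|---|---|
| 0 | 0.993 to 0.997 | 0 |
| 0.1 | 1.00 to 1.02 | 0.015 to 0.04 |
| 0.2 | 1.01 to 1.12 | 0.03 to 0.08 |
| 0.3 | 1.03 to 1.52 | 0.05 to 0.12 |

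For comparison, the standard error is about 0.17 to 0.25 kPa and the target difference is 0.8 kPa. A separate simulation with residual SD 1.0 and correlation 0.6 gave 1.02 to 1.03 at a gap of 0.2, and 1.08 to 1.10 at 0.3.

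**Average bias.** With complete data it was zero within simulation error (at most 0.009 kPa). When month-6 dropout was made to depend strongly on baseline, in opposite directions in the two arms, the shared-slope model was biased by about 0.08 to 0.14 kPa for gaps of 0.2 to 0.3. One of these runs used about 15% dropout, against the planned 10%. Adding baseline by time removed the bias (at most 0.01 kPa remained in that run).

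**The case against.** The strongest reply is that the article says only that the model is adjusted for baseline and does not give the form of that adjustment. A condensed article may leave a baseline interaction to the analysis plan, and a single-slope adjustment is a legitimate model. This stands in part: the unseen plan may already contain the term. But the article lists the terms twice and names the interactions it wants, so the model as stated has one slope.

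The second reply is that nothing is lost unless the slopes differ, and the document gives no slope, baseline SD or between-visit correlation. This stands in full. With equal slopes the shared-slope model is slightly the more precise.

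Three stronger readings are tempting, and the document supports none of them.
- A reader might infer that unequal slopes follow from selecting people on the same single reading that serves as baseline. Measurement error in that reading attenuates both slopes alike and does not by itself separate them.
- A reader might infer that three further months of treatment must weaken the slope. That happens only if the treatment effect depends on baseline; an additive effect leaves the slope unchanged. A longer interval makes a gap plausible, not established.
- A reader might infer that the trial falls short of its stated power. With the plan's 0.8 kPa, an SD of change of 1.0 and 31 per arm, simulated power stayed at or above 0.88 in every setting.

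**Conclusion.** The point holds as a minor, conditional one. As written, the month-6 contrast is corrected for baseline with a slope of which half or more can come from month 3. If the visit slopes differ by 0.2, the variance of the contrast rises by about 1 to 12%. If they differ by 0.3, it rises by about 3 to 50%, and about 10% in typical settings. Part of any chance imbalance then remains in the estimate, usually well below one standard error. These sizes rest on the assumed baseline SD, residual SD ratio and correlation, none of which the document gives.

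The shared slope does not invalidate the randomised comparison: with complete data it is unbiased on average. Bias needs both unequal slopes and dropout that depends on baseline differently by arm. The simulated case was deliberately strong, and nothing in the document shows that such dropout will occur.

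**What to change.** Add baseline LSM by time point as a fixed effect in the primary model, so that the T2 contrast uses the month-6 baseline slope. Do the same in each secondary model measured at both follow-up visits, using that outcome's own baseline value. State this before the data are analysed. If the analysis plan already contains the term, nothing further is needed.

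The cost is one degree of freedom per outcome and, if the slopes turn out equal, at most about 1% of variance. It needs no new data and no change to the sample size.

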### Monitoring

An independent monitor (quality officer), appointed by the sponsor, will monitor the study data according to Good Clinical Practice (GCP). The frequency of the monitoring is related to the risk of the investigation. For at least a selection of the participants, informed consent forms will be checked. Source Data Verification will minimally be performed (checking if data from the Case Report Forms (research forms/questionnaires) match with the source data (patient status, results, etc)). The quality of data will be guaranteed by using the data management software Castor EDC. The monitor will check whether all (Serious) Adverse Events (S)AEs and Suspected Unexpected Serious Adverse Reactions are adequately reported within the timelines as required by law, the presence and correctness of the informed consent forms, the delegation log and the data storage.

### Adverse events reporting and harms

Adverse events are defined as any undesirable experience occurring to a participant during the study, whether or not considered related to the intervention. All adverse events reported spontaneously by the participant or observed by the investigator or staff will be recorded in the case report forms.

A serious adverse event is any untoward medical occurrence or effect that

results in death;is life threatening (at the time of the event);requires hospitalisation or prolongation of existing inpatients’ hospitalisation;results in persistent or significant disability or incapacity;is a congenital anomaly or birth defect; orany other important medical event that did not result in any of the outcomes listed above due to medical or surgical intervention but could have been based on appropriate judgement by the investigator.

An elective hospital admission will not be considered as a serious adverse event.

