#### Diet group

Participants in the diet group will follow with a calorie restricted Mediterranean diet, with an eating window between 8 am and 6 pm for a period of 6 months. Participants are asked to stop eating at 6 pm. This results in a daily fasting window of approximately 14 hours. During the fasting time, only calorie-free drinks will be allowed. A daily calorie restriction of 500 kcal will be applied, based on the estimated energy requirement calculated using the WHO equation for participants with a BMI ≤30 and the Harris-Benedict equation for those with a BMI >30.^26^ The diet will be based on the Mediterranean food pyramid,^27^ emphasising high-fibre foods such as fresh fruits and vegetables, unprocessed whole grains, beans, seeds, herbs and spices, while limiting processed foods, red meat, sweets and alcohol. At baseline, participants receive a detailed explanation of the dietary protocol, two sample daily meal plans, recipes and a food-exchange list. Dietary adherence is assessed at the 3-month and 6-month follow-up visits using food diaries in which participants record all foods consumed and the corresponding times. The eating window is additionally evaluated at each visit through a questionnaire assessing the average latest eating time and the number of days per week participants adhere to the fasting regimen. Participants receive guidance from a registered dietitian to support correct implementation of the intervention. Consultations take place during the in-person study visits at baseline, 3 months and 6 months. Throughout the intervention period, participants may also contact the study dietitian by telephone for ongoing support. During the entire programme, 60 min of exercise per day is advised. Physical activity will be measured for 1 week with the Activ8 Activity Tracker GEN2 at baseline and at the end of the study.

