#### Medication group

The medication used in the study is N/B to ensure that the comparator reflects weight loss alone, without any additional metabolic or liver-specific pharmacological effects. Participants in the medication group will take N/B (Mysimba) two times per day at a total dose of 32 mg/360 mg N/B per day for a duration of 6 months. The dosage will be built up in the first month following the stepped care approach used in the Summary of Product Characteristics (SmPC), up to maximally tolerated doses. Compliance with N/B intake is monitored by pill counting at the 3-month and 6-month visits. Participants are asked to bring all medicine packaging to each visit, and the number of remaining tablets is recorded by the researcher. Adherence is defined a priori as taking at least two tablets per day, with dose adjustments permitted based on individual tolerance. They receive usual care, including the advice of 60 min of exercise per day and standard dietary recommendations according to the guidelines for the Dutch population.^28^ During the visits at baseline, 3 months and 6 months, medication use and usual care will be evaluated by a physician in the hospital. Participants will wear the Activ8 Activity Tracker GEN2 at baseline and at the end of the study.

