### Outcomes

The main study parameter is the between-group difference in absolute change in liver fibrosis during 6 months. Liver fibrosis will be measured as LSM (kPa) by transient elastography (FibroScan).

Secondary study parameters are as follows:

Absolute change in liver steatosis (Controlled Attenuation Parameter score, FibroScan).Nutritional assessment: body weight (kg, Seca 888 compact digital flat scale), height (cm), waist circumference (cm), fat mass and lean body mass measured with bioelectrical impedance analysis (kg, Bodystat 500), grip strength (kg, Jamar).Cardiovascular risk factors: total cholesterol, low-density lipoprotein cholesterol, high-density lipoprotein cholesterol, triglycerides, apolipoprotein B (ApoB), apolipoprotein AI (ApoAI), lipoprotein (a), Hemoglobin A1c, fasting blood glucose, fasting insulin and blood pressure, measured with routine lab procedures.Other laboratory measurements, measured with routine lab procedures. Among others, the following routine measurements will be done: creatinine, eGFR, alanine aminotransferase (ALAT), aspartate aminotransferase (ASAT), thrombocytes, haemoglobin (Hb), leucocytes, transferrin, ferritin, total iron binding capacity, apolipoprotein B48 (ApoB48), fibroblast growth factor 19 (FGF19) and 21 (FGF21), C-reactive protein (CRP), fibrosis-4 index score (Fib-4), thyroid-stimulating hormone (TSH), free thyroxine 4.Physical activity (Activ8 Activity Tracker GEN2).Quality of life (36-Item Short Form Health Survey Questionnaire).^29^Patient satisfaction in case of T2D (Diabetes Treatment Satisfaction Questionnaire).^30^Food intake and adherence to the dietary intervention (3-day food diary).Demographic variables, drug use, smoking and drinking habits, medication use and compliance to the time restriction (self-developed questionnaire).

Other study parameters are as follows:

Shift in liver fibrosis severity (categorised in fibrosis score F0-F3).Side effects (self-reported).Number of participants that drop-out (categorised by reason for drop-out).

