### Data collection

The recruitment, enrolment and data collection are conducted by the investigator, who is also responsible for delivering the interventions. Before the start of the study, the investigator will hold a pre-screening by phone to explain the study and discuss the inclusion and exclusion criteria. The patient is given at least 2 weeks for reflection. If the patient agrees to participate, a screening will be scheduled at the Franciscus hospital to determine the degree of liver fibrosis using transient elastography (Fibroscan).

If the participant meets the inclusion criteria, they will sign a consent form together with the researcher during the same visit, and the baseline measurements and randomisation will be performed. After 3 months (visit 2) and 6 months (visit 3), the same measurements are performed as at baseline (visit 1) (table 1). Participants in both groups will have an appointment by phone with the researcher after 2 weeks to check whether the diet or medication is being used properly and whether complaints have occurred.

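### After the 2-week call the article describes no identical symptom enquiry in the two arms, so side-effect counts may not be comparable between diet and N/B

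*Protocol article*

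**What the plan says.** The Outcomes section of the protocol article lists "Side effects (self-reported" under the other study parameters, after the primary and secondary ones. The section on adverse events reporting and harms gives the capture rule: "All adverse events reported spontaneously by the participant or observed by the investigator or staff will be recorded in the case report forms".

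One active enquiry is common to both arms. The Data collection section describes it as a phone contact between participant and researcher 2 weeks after the start, in either arm. Its stated purpose is to "check whether the diet or medication is being used properly and whether complaints have occurred".

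At the study visits the described contact depends on the arm:

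- **N/B arm** (Medication group): at baseline, 3 and 6 months, "medication use and usual care will be evaluated by a physician in the hospital". The same section lets the dose be adjusted to individual tolerance.
- **Diet arm** (Diet group): "Participants receive guidance from a registered dietitian to support correct implementation of the intervention". This happens at the same three visits as the physician contact in the N/B arm. Outside the visits, the section adds that "participants may also contact the study dietitian by telephone for ongoing support".

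The Randomisation section states that participants are not blinded. Table 1 has no side-effect or adverse-event row. The self-developed questionnaire, completed by both arms at baseline, 3 and 6 months, is described under Outcomes as covering demographics, substance and medication use, smoking, drinking and keeping to the eating window. Symptoms are not among the listed contents.

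**The concern.** The Introduction names nausea, constipation, vomiting, diarrhoea and dry mouth as possible effects of N/B. Staff can rarely observe these, so under the stated rule their recording depends mainly on the participant mentioning them. Whether a participant does so depends on what is discussed at the visit and on what the participant expects, and both can differ between arms in an unblinded trial.

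The trial is meant to inform the choice between a diet and a drug. Readers of a two-arm report will set the side-effect rates side by side even though the article plans no test of them. If capture differs, part or all of an observed difference could reflect how symptoms came to be recorded. Milder symptoms arising after week 2 may also go unrecorded in either arm, and these could help to explain reduced dosing or poor adherence.

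**Working it through.** The article states no figure on this point, so there is nothing to reproduce. The check has two parts.

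**1. Opportunities to record a symptom, by arm**

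| Time | N/B arm | Diet arm | Same enquiry described? |
|---|---|---|---|
| 2 weeks | Researcher call, asks about complaints | Researcher call, asks about complaints | Yes |
| 3 and 6 months | Physician, on medication use and usual care | Dietitian, on carrying out the diet | No |
| Between visits | None described beyond the 2-week call | Optional calls to the dietitian | No |
| Any time | Spontaneous report or staff observation | Spontaneous report or staff observation | Same rule, but passive |

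The Medication group section builds the dose up over the first month, so the one shared enquiry takes place before build-up ends. A medication review in which dose depends on tolerance is likely to touch on symptoms. No counterpart is described for the diet arm. The optional dietitian calls are an extra route in the diet arm only, so the direction of any imbalance is not certain.

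**2. What unequal capture could do (illustration)**

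Inputs: 35 participants per arm (Sample size and recruitment). The true rate p, equal in both arms, and the capture probabilities c are assumptions, because the documents give neither.

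Formulas:
- observed rate = p × c
- observed risk ratio = (p × c₁)/(p × c₂) = c₁/c₂
- SE of the difference = √[a(1−a)/35 + b(1−b)/35], where a and b are the observed rates

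| p | c₁ / c₂ | a | b | Difference | Risk ratio | SE |
|---|---|---|---|---|---|---|
| 0.20 | 0.9 / 0.7 | 0.18 | 0.14 | 0.04 | 1.29 | 0.088 |
| 0.30 | 0.9 / 0.7 | 0.27 | 0.21 | 0.06 | 1.29 | 0.102 |
| 0.40 | 0.9 / 0.7 | 0.36 | 0.28 | 0.08 | 1.29 | 0.111 |
| 0.20 | 0.9 / 0.5 | 0.18 | 0.10 | 0.08 | 1.80 | 0.082 |
| 0.30 | 0.9 / 0.5 | 0.27 | 0.15 | 0.12 | 1.80 | 0.096 |
| 0.40 | 0.9 / 0.5 | 0.36 | 0.20 | 0.16 | 1.80 | 0.106 |

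In participants, the last row is 0.36 × 35 = 12.6 against 0.20 × 35 = 7.0, with no true difference.

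If someone applied a two-sided 5% test to such counts, the chance of a significant excess in the better-captured arm would be about 7–11% with 90%/70% capture and 16–32% with 90%/50%. With equal capture it would be about 2.5% in that direction.

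The risk ratio is simply the ratio of the two assumed capture probabilities. The table shows how sensitive the counts are to unequal capture. It does not show that capture is unequal in this trial.

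**The case against.** The strongest reply is that a journal article condenses the protocol, and the form used to elicit side effects is the kind of detail left to the full document. Table 1 is not exhaustive: it also omits the diabetes treatment satisfaction questionnaire and the 2-week call. The missing row therefore proves little, and an unseen case report form may contain a common enquiry. That limits the point but does not remove it, because the article states a rule, and the rule it states is unsolicited.

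Four stronger readings are tempting, and the documents do not support them.

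- **That side effects are captured only when volunteered.** Staff observation also counts, and the 2-week call asks both arms.
- **That tolerability is a planned between-arm outcome.** Side effects are an other parameter. No objective names them, and the Statistical methods section describes models for the primary and secondary outcomes only.
- **That the counts are tilted towards N/B by who asks.** The physician's stated subject is medication use and usual care, not adverse events. Data collection is assigned to the investigator, with no difference by arm. The tilt is an inference.
- **That diet participants have no reason to report symptoms.** The adverse event definition covers any undesirable experience, related to the intervention or not. Drop-out is also recorded by reason, so symptoms severe enough to end participation have another route into the data.

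**Conclusion.** The point holds as a risk to comparability. After week 2 the article describes no enquiry about symptoms that is the same in both arms, visit contact differs by arm, participants are unblinded, and the stated rule is passive. Side-effect rates could then differ without any true difference. The size is unknown. Under the assumed capture probabilities the spurious risk ratio is 1.29 to 1.80, or 4 to 16 percentage points when the true rate is 20–40%. It could run in the other direction if capture were better in the diet arm.

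A larger assumed gap would give a larger ratio, for example twofold with 80% against 40% capture, but that only restates the assumption and is not evidence about this trial. The primary and secondary outcomes are untouched. The change is worth making because it is cheap and the side-effect table will be read comparatively, not because a bias has been shown.

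**What to change.** Add one short symptom checklist, identical in both arms, to the questionnaire that all participants already complete at baseline, 3 and 6 months, and use the same list at the 2-week call. Include the five effects named in the Introduction and a set of symptoms relevant to fasting, each with presence and severity. Report solicited symptoms descriptively by arm, separately from AE and SAE reporting, which stays as it is.

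The cost is about ten items and one table, with no new visit or staff. There are two downsides. Solicited rates will be higher than spontaneous ones in both arms. Also, the study started in April 2025, so participants already enrolled will have no baseline checklist. For them, report presence at follow-up rather than new onset, and state how many are affected.

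If the case report form already contains a common enquiry, no new instrument is needed. The section on adverse events reporting and harms should then be aligned with it.
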